## 3. Interventions and Procedures

### 3.1. Intervention Groups

#### 3.1.1. Development of Interventions

The intervention procedures have been developed by (1) applying the framework of exercise programs proposed by the American College of Sports Medicine (ACSM) [38]; (2) constructing domain-specific content for physical exercise interventions via a review of the existing literature for young children [7,26,27,31,37]; (3) obtaining open-ended responses concerning how preschool children exercise to improve FMSs and PF from preschool education experts and teachers; (4) constructing the actual intervention procedures; and (5) examining the validity of factor structures underlying the intervention procedures by consulting other preschool education experts and teachers and conducting pilot studies.

A review of previous studies shows that physical games (aerobic games, ball games, etc.), rhythmic activities, sports (basketball, football, swimming, etc.), fundamental movements activity (gross motor movements, functional movements, etc.), aerobic training, and comprehensive physical exercise were used in FMSs and PF intervention programs for children aged 4–5 years, and proved to be superior to free play or unorganized physical activity [25,29,31]. The results of interviews with preschool education experts and teachers, and the restrictions of the Ministry of Education of the Chinese government on the implementation of standardized “curriculum” and competitive sports in kindergartens were considered [39]. Ball games, rhythmic activities, basic movements, and multiple activities are the physical exercise programs of this study.

#### 3.1.2. Contents of Interventions

Each of the four interventions is based on structured lessons, which will involve a 30-min lesson three times per week for 16 weeks. In all four groups, each lesson will consist of a 5-min warm-up, 20 min of core exercises, and a 5-min cool-down activity. The warm-up will consist of light-intensity movements (e.g., wrist rotation and leg swing), moderate-intensity activities (e.g., arm rotation and knee-up walk), and higher-intensity activities (e.g., arm sprint and on-site running); cool-down will start with moderate-intensity activities and end with light-intensity movements. The main part of the lesson will include 5 min of moderate-to-vigorous intensity activity according to the respective intervention procedures, with at least 2 min of vigorous-intensity activity, every 10 min [40,41]. The four interventions will be carried out in the form of games to increase children’s interest, and will only differ in the main part (Table 1). The intervention will be carried out within the PA plan of kindergartens, to avoid extra PA for the preschool children in the intervention groups.

### 3.2. Control Group

To avoid the impact of activity experience on the FMSs and PF of preschool children in the control group, preschool children in the control group will participate in “unorganized PA”, while the intervention groups will participate in the designed lessons. The unorganized PA in this protocol is defined as: (1) children perform PA without the instructions of teachers, who are only responsible for the safety of children; (2) the types and intensity of activities are not affected by the teachers; (3) competitions that are spontaneously organized by young children, such as racket, dribbling, and balance beam competitions, are also unorganized PA. The PA content of the control group will be reported by their teacher once a week to ensure that the PA content of preschool children in the control group meets the requirements of the intervention program.

#### 3.2.1. Delivery and Fidelity Check of Interventions

Before the beginning of the formal intervention study, a workshop for PEFP members and a pilot study will be carried out to examine (1) the contents of the training program for interventionists and (2) the feasibility of intervention programs.

The formal physical exercise intervention will be implemented by kindergarten teachers participating in this study, and teachers will receive a two-hour training before the intervention at the kindergarten or university location. The training will be carried out with a prepared intervention portfolio, presentations, and visual materials. Following the training, a guided interview will be conducted by a second researcher to obtain information regarding (a) teaching and mediation competence using methods and materials, with consideration of the preschoolers’ characteristics; (b) whether the interventionist will implement the interventions as planned; and (c) any comments on improvements in the training and general remarks.

In the pilot study, each interventionist will carry out the physical exercise intervention lessons according to the randomized group and provide feedback on the feasibility of the lessons according to different criteria (time, content, goals, etc.) using a checklist provided by the researchers. Each intervention group will be assigned an additional researcher to supervise the quality of the intervention. In addition, the researcher will also play a protective role and record any special situations (accidental injuries) that occur during the intervention.

In addition, the PEFP members will also keep in close touch with preschool teachers via instant networking software. So, throughout the execution of the study, we will share information and solve potential problems in a timely fashion. First, files and videos of the intervention procedures will be distributed to class instructors or teachers ahead of time to remind them of the contents that are going to be implemented. Second, the teamwork group will help solve the problems encountered online.

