#### 3.2.2. Conditions for Termination of Intervention

The injury risk associated with the intervention content in this study is low, and few injury events have been reported in similar studies [36]. During implementation, unless injured child(ren) are affecting the conduct of the intervention or other irresistible factors, the intervention will continue as planned. The intervention and data analysis will be conducted according to an intention-to-treat analysis. The data of all the enrolled participants will be analyzed; the missing data will be processed using the mean interpolation method. If injury to a child occurs during the course, the kindergarten, parents, and research leader will jointly negotiate the treatment plan. The FMSs and PF of all subjects will be assessed before and after the intervention, and at the end of the 6-month follow-up. The results of the follow-up will be used for auxiliary analysis. Consent to participate in this program will be obtained from the recruited children’s parents, and the children can quit at any time. If the intervention is terminated due to irresistible external factors (such as suspension of classes due to COVID-19), the intervention duration will be extended or another time will be chosen to restart the intervention according to whether the intervention is terminated for more than 2 weeks. All decisions will be made by the project leader.

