### 4.3. Data Management

All research data entry will be carried out by two people, followed by an interrater consistency check. Consent forms will be stored separately from participant data, and a unique identifier code will be assigned to each participant. Data will be deleted immediately from voice recorders after the transcription, with pseudonyms used in all reports in place of participants’ names. Data will only be accessible to primary researchers and statisticians after application to the research group. Data will be stored for a maximum of 5 years before being securely destroyed.

All phases of this study will be monitored by a data safety officer, who has worked for monitoring data collection and data analysis. The data safety officer is responsible for the data management and distribution of applied data, and will not obtain the details of the research. Management of the trial data will be in accordance with the data management plan, which was developed and approved by the project group. Moreover, the data will be published in two ways: writing academic papers and uploading to the experiment registration website.

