## 7. Challenges and Limitations

The current protocol has some challenges. First, the participants in this study are 4-–5-year-old preschool children who still largely lack self-control and attentional focus. It will, therefore, be difficult to engage them continuously in the designed physical exercise program. To meet this challenge, the research group will staff each intervention group with two researchers to ensure preschool children’s safety and the intervention quality. Second, the intervention will last for 16 weeks, which will place a great human resource pressure on the PEFP group. We plan to stagger the intervention time of two close kindergartens, and the intervention will be carried out between 8:30 and 11:30 in the morning. In this way, the researchers assigned by the PEFP group can assist more intervention groups within the time allowed.

There are some limitations to this protocol. First, young children are in a rapid period of growth and development; thus, it will be difficult to identify whether natural growth or the exercises intervention contributes to the improvement in children’s FMSs and PF. Like other studies, this protocol will set up a control group in the same school with each intervention group to reduce the confounding impact of natural growth as much as possible. Second, the intervention in this study will last 16 weeks, which seems insufficient to improve FMSs and PF. However, the duration of FMSs or PF interventions in previous studies varied from eight weeks to one academic year or longer [32,41,52,53].

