Cardiorespiratory fitness	20-m shuttle-run	Materials: flexible rulers, marking tap, poles, and stopwatch. Site layout: two parallel lines 20 m apart will be marked on the floor using marking tap.	Child will be instructed to run progressively to exhaustion from one line to another 20 m apart, changing direction at the pace set by an audio signal that increases progressively.	The test ends when the child fails to reach the end lines concurrent with the audio signal on two consecutive occasions or when the child stops because of exhaustion.	Testers will be continually encouraging participants so that they give their best performance. Child performs a test no longer than 8–10 min.

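### The only stated injury recording is attached to the intervention groups, so an injury table by arm would be unequally ascertained and tilted against the programmes

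*Protocol article*

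**What the plan says.** **Intervention groups.** Section 3.2.1 provides that "Each intervention group will be assigned an additional researcher to supervise the quality of the intervention" and adds that "the researcher will also play a protective role and record any special situations (accidental injuries) that occur during the intervention". Both sentences stand in a paragraph introduced as describing the pilot study. Section 7 returns to staffing, again for the intervention groups only and partly for the children's safety: "the research group will staff each intervention group with two researchers".

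**Control group.** Section 3.2 defines the control condition as one in which "children perform PA without the instructions of teachers, who are only responsible for the safety of children". Competitions that the children start themselves, including on a balance beam, count as control activity. On reporting, the section says: "The PA content of the control group will be reported by their teacher once a week". Its stated purpose is to check that the content meets the requirements of the programme.

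**If a child is injured.** Section 3.2.2 calls the injury risk of the intervention content low, with reference to similar studies. It then says: "If injury to a child occurs during the course, the kindergarten, parents, and research leader will jointly negotiate the treatment plan". This concerns how treatment is agreed, not how an injury is recorded or tabulated.

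**Test rounds.** All arms are tested at three time points (Section 3.2.3). In the 20-m shuttle run of Table 3, "Child will be instructed to run progressively to exhaustion from one line to another 20 m apart". Table 2 asks testers to protect the child on the beam, and Section 4.2 includes emergency plans in tester training. No injury record is mentioned.

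**Oversight.** Section 4.3 has a data safety officer monitor every phase, gives that officer data-management tasks, and adds that the officer "will not obtain the details of the research".

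**The concern.** Harms can be compared between arms only if they are looked for in the same way in each arm. Here the article fixes a different procedure by arm: an extra person with a duty to record in the programme groups, and a report confined to activity content in the control group. Control is not a safe zero. Uninstructed play with spontaneous competitions can plausibly cause injuries, and these would have no stated way into the data.

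The abstract intends the most effective programme to be taken up by kindergartens, and Section 3.2.2 describes the risk as low. A reader of the results would want to see that description beside ordinary play. With unequal capture, a programme no riskier than free play could look more harmful, so the sponsor itself has an interest in equal recording.

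**Working it through.** The article states no injury rate and plans no harms analysis, so there is no figure to reproduce. The check sets the sections side by side, followed by short arithmetic.

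**1. Who records, where and when**

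| Setting | Person present with a safety role | Recording stated |
|---|---|---|
| Lessons, four intervention arms | Researcher (3.2.1, 7) | Accidental injuries (3.2.1, in the pilot paragraph) |
| Control sessions | Class teacher (3.2) | Weekly activity content only (3.2) |
| Test rounds, all arms | Trained testers (4.2, Table 2) | None stated |

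**2. Two readings of the pilot paragraph**

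- If the duty carries into the main trial, recording is stated for four arms and not for the fifth.
- If it covers the pilot only, the main trial has no stated recording in any arm. The imbalance disappears, but so does the record.

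The text does not settle which is meant. Either way it needs a statement for the main trial.

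**3. Direction of the bias under the first reading**

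Observed rate ratio (programme to control) = true rate ratio × (share of injuries captured in programme ÷ share captured in control).

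The second factor is 1 with equal capture. It rises without limit as control capture falls towards zero. With less complete capture in control, the observed ratio is too high. Neither share can be had from the document, so no single figure can be given.

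**4. Exposure**

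- Lessons per class: 3 per week × 16 weeks (Section 3.1.2) = 48.
- Children per arm: about 60 (Section 4.1).
- Child-sessions per arm: 48 × 60 = 2,880. Over four intervention arms: 4 × 2,880 = 11,520. Control, which runs alongside the lessons: about 2,880.

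These are nominal exposures before drop-out, not counts of observed sessions.

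**5. What equal recording could and could not show**

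With zero injured children, the one-sided 95% upper bound on risk per child is 1 − 0.05^(1/n):

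- control, n = 60: 1 − 0.05^(1/60) = 4.9%
- pooled programmes, n = 240: 1 − 0.05^(1/240) = 1.2%

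Power for 60 against 240 children, two-sided 5%, is Φ[(Δ − 1.96 × SE₀)/SE₁], with SE₀ from the pooled risk and SE₁ from the separate risks. For an assumed 5% in control and 10% in the programmes:

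- pooled risk = (60 × 0.05 + 240 × 0.10)/300 = 0.09
- SE₀ = √[0.09 × 0.91 × (1/60 + 1/240)] = 0.0413
- SE₁ = √[0.05 × 0.95/60 + 0.10 × 0.90/240] = 0.0342
- power = Φ[(0.05 − 0.0810)/0.0342] = Φ(−0.91) = 18%

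| Assumed control risk | Power, doubling | Power, tripling |
|---|---|---|
| 1% | 4% | 7% |
| 3% | 10% | 29% |
| 5% | 18% | 55% |
| 10% | 43% | 94% |

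Clustering is ignored, so these values are optimistic. Equal recording supports description and upper bounds. It does not support a test.

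**The case against.** The strongest reply is that much of this rests on silence in a condensed article. Section 4.3 refers to a separate data management plan that is not shown, and injury forms may be there. Control teachers do have a safety duty, and the injury sentence in Section 3.2.2 is not expressly limited to one arm. No harms outcome or harms comparison is planned in Sections 3.3 or 4.4, so no stated objective fails. Even with equal recording, power would be low.

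Most of this stands, and it limits the point. It does not remove it, because the article goes beyond silence: it names who records, for which groups, and what the control teacher reports. Those statements differ by arm.

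A reader might also infer four stronger things that the document does not support:

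- **That injuries in control go unrecorded and harms cannot be compared at all.** The text states no recording there. It does not exclude it.
- **That the test rounds add to the bias.** All arms take the same tests on the same schedule, so a missing record there does not in itself favour any arm. It is a gap in completeness.
- **That the data safety officer is denied injury reports.** The role reads as data management, and the phrase about details may refer to masking. Nothing says that injury information is withheld.
- **That one researcher in Section 3.2.1 contradicts two in Section 7.** The first passage speaks of an additional researcher, and each group has two classes (Section 4.1), so the two statements can be compatible.

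**Conclusion.** The point holds in limited form. As written, the only stated injury recording sits with the intervention groups, and the control report covers activity content only. If the recording applies to the main trial and injuries are tabulated by arm, the table would be biased against the programmes. The bias has a known direction and an unknown size, over about 2,880 child-sessions in each arm. This assumes that a dedicated observer captures more than a teacher who has not been asked to report injuries, and that no unseen document already equalises recording. If the duty is confined to the pilot, the problem is instead that the main trial has no stated recording in any arm. No planned efficacy analysis is affected. This is an inexpensive improvement worth making before the intervention starts, because data not collected alike cannot be repaired afterwards.

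**What to change.** 1. In Section 3.2.1, state that injury recording applies to the main trial.
2. Have the teacher of every class in all five arms complete the same short injury item each week. For control it is a line on the existing weekly report. Intervention classes are not now stated to send such a report, so for them it is new.
3. Keep the researcher's note as a separately labelled additional source, so that the comparison between arms rests on the item common to all.
4. Put the same item on the test sheet for the three rounds.
5. Name who reviews the log.
6. Report injuries descriptively per child-session by arm, with no claim of power.
7. In Section 4.3, say whether the sentence on the officer's access to details refers to masking.

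The cost is about a minute of teacher time per class per week, one new short form for the intervention classes, and one line on the test sheet. Sample size, outcomes and the primary analysis do not change.

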#### 3.2.2. Conditions for Termination of Intervention

The injury risk associated with the intervention content in this study is low, and few injury events have been reported in similar studies [36]. During implementation, unless injured child(ren) are affecting the conduct of the intervention or other irresistible factors, the intervention will continue as planned. The intervention and data analysis will be conducted according to an intention-to-treat analysis. The data of all the enrolled participants will be analyzed; the missing data will be processed using the mean interpolation method. If injury to a child occurs during the course, the kindergarten, parents, and research leader will jointly negotiate the treatment plan. The FMSs and PF of all subjects will be assessed before and after the intervention, and at the end of the 6-month follow-up. The results of the follow-up will be used for auxiliary analysis. Consent to participate in this program will be obtained from the recruited children’s parents, and the children can quit at any time. If the intervention is terminated due to irresistible external factors (such as suspension of classes due to COVID-19), the intervention duration will be extended or another time will be chosen to restart the intervention according to whether the intervention is terminated for more than 2 weeks. All decisions will be made by the project leader.

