#### 3.2.3. Measurement Slots

Participants will be assessed three times: at baseline, the end of the intervention, and the end of the 6-month follow-up. At each time point, we will assess participants’ FMSs, PF, PA, and descriptive data (such as age, sex, weight, height) within one week. The executive plan of FMSs and PF is outlined in Figure 2.

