## 4. Statistical Analysis

### 4.1. Sample Size

The primary outcome variables in this study are FMSs and PF. Before recruitment, a priori power analysis was performed in G*Power 3.1 to calculate the sample size necessary to detect meaningful changes from the baseline to the post-intervention time points in the total raw scores of seven FMSs (i.e., 10-m shuttle-run, hopping, bouncing a ball, jamming coins, kicking, balance beam, and one-leg stand) and seven PF (i.e., balance beam, handgrip, standing long jump, sit-and-reach, 10-m shuttle running, 20-m shuttle running, handgrip strength, and hopping). Using an alpha of 0.05 and a power of 80%, the calculation of the power to detect a pre-post change in these measures was based on the effect sizes reported in a recent systematic review. The expected effect size of the intervention on FMSs and PF was at 1.42 and 0.36 (standardized mean difference, SMD), respectively [51]. With reference to these results, a prudent estimation of the effect size (SMD = 0.36) was used for the calculation. The required sample was calculated to be 70. To account for the clustering effect, this number was then multiplied by a design effect (DE) of 1 + (*m* − 1) × ICC, where *m* is the average cluster size and ICC was estimated at 0.05. With an estimated average class size of 30, at least 150 participants will have to be recruited. Based on previous studies, we presumed a drop-out rate of 15%, implying a minimal sample size of 150/0.85 = 176 children in total. This study takes the class as the cluster of random sampling; the class size in recruited kindergartens is 30–35. Therefore, considering the drop-out rate and special samples (preschool children with developmental retardation or hyperactivity disorder), each experimental group was divided into two classes, implying about 60 children in each group. The total size is 300.

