### 4.4. Data Analysis Plan

Baseline characteristics and unadjusted study outcome measures will be summarized by intervention groups using descriptive statistics and used to assess between-group equivalence at baseline. Prespecified baseline covariates in both primary and secondary outcome analyses will include age, sex, FMSs capacity, PF level, and PA level.

Baseline demographic descriptors and primary and secondary outcome measures will be compared across groups by using analysis of variance (a non-parametric test will be used when the data does not conform with a normal distribution) for continuous variables and the χ^2^ test for categorical variables. The planned descriptive data on measured-point FMSs and PF will be tabulated across the intervention groups and control group. In our primary analysis of the FMSs and PF outcome, we will use mixed model analyses to estimate the differences with their corresponding 95% CIs, comparing the BA, RA, BM, and MA groups with the control group. Time, physical exercise programs (intervention or control groups), and their interaction will be fixed factors. The random effects will be the kindergarten and individual to take into account the clustered data structure.

Multilevel linear regression models will be constructed to assess the effectiveness of the physical exercises on FMSs and PF performance. The baseline data of the outcome variables, assessment points, intervention groups, and any imbalanced covariance will be added to the model along with the kindergartens and PA as random effects. The interaction between physical exercise and FMSs and PF will be tested.

Secondary analyses will investigate the effect of the intervention on other domains using different types of regression analyses, depending on the outcomes. Logistic regressive analyses will be constructed to assess the interference factors. The models will be used to assess the effect of forms of physical exercise, and to explore associations between secondary outcome measures, and will be adjusted for various confounding factors (e.g., sex, PA).

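### Section 3.2.2 fixes single mean imputation without saying which mean; the filled values count as observed, so standard errors or effects are distorted depending on the reading

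*Protocol article*

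**What the plan says.** Section 3.2.2 commits to intention to treat: "The data of all the enrolled participants will be analyzed". The same sentence adds that "the missing data will be processed using the mean interpolation method". It gives no definition of the mean, no assumption about why data are missing, and no distinction between outcomes and covariates.

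Section 3.2.3 sets the visits: "Participants will be assessed three times: at baseline, the end of the intervention, and the end of the 6-month follow-up". Section 4.1 expects the loss: "we presumed a drop-out rate of 15" per cent.

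Section 4.4 gives the primary analysis: "we will use mixed model analyses to estimate the differences with their corresponding 95% CIs". Its structure is "Time, physical exercise programs (intervention or control groups), and their interaction will be fixed factors", and "The random effects will be the kindergarten and individual to take into account the clustered data structure". A further model conditions on baseline: "The baseline data of the outcome variables, assessment points, intervention groups, and any imbalanced covariance will be added to the model". Section 4.4 also prespecifies age, sex and baseline FMSs, PF and PA as covariates. It does not mention the imputation rule, so nothing in the article qualifies that rule.

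**The concern.** A filled-in mean carries no information about the child it stands for, yet the model counts it as a measurement. The damage depends on which mean is meant. A mean taken within the arm leaves the arm difference alone but understates its standard error. A mean taken over all children pulls the arms together.

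The rule also sits badly with the planned model. A mixed model with time, group, their interaction and a random effect for the child uses every observed visit, and is valid for outcomes missing at random without filling any in. Imputing means first gives up that property and alters the variance components behind the 95% confidence intervals. At stake are the estimate and interval of each comparison of an exercise arm with control.

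**Working it through.** **Inputs from the article.** Drop-out q = 0.15, alpha 0.05 (two-sided assumed), SMD 0.36, ICC 0.05, class size 30, two classes and about 60 children per arm (section 4.1); three assessments (section 3.2.3).

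**Inputs assumed.** Pre-post correlation 0.6 in the pre/post simulations; the mean actually used; the missingness mechanism.

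**The plan's own figure.** The only stated number that uses the loss rate is 150/0.85 = 176.5, given as 176. It reproduces to rounding. At 15% loss, 0.15 × 60 = 9 children per arm would carry filled values.

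**Arm mean, missing completely at random.**
- True SE of the arm difference: σ√[2/(n(1−q))].
- After filling, the difference is unchanged, the sample variance falls to about σ²(1−q), and n is counted in full. The reported SE is σ√(1−q)·√(2/n).
- Ratio reported/true = √[(1−q)(1−q)] = 1−q = 0.85.
- Type I error = 2[1−Φ(1.96 × 0.85)] = 9.6%. The same formula gives 6.3% at 5% missing and 14.2% at 25%.

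**Overall mean, missing completely at random.** The effect is multiplied by 1−q: 0.36 × 0.85 = 0.306. The SD is multiplied by √0.85 = 0.92.

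**Simulation, 60 v 60, no class effect, 15% of post values missing completely at random** (ANCOVA 4,000 runs; time-by-group contrast 10,000 runs):

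| Handling | Model | Mean effect (true 0.36) | Model SE / empirical SE (no effect) | Type I error |
|---|---|---|---|---|
| Arm mean | ANCOVA | 0.361 | 0.141 / 0.164 | 9.1% |
| Arm mean | time × group | 0.360 | 0.166 / 0.182 | 7.5% |
| Overall mean | ANCOVA | 0.303 | 0.140 / 0.138 | 4.9% |
| Overall mean | time × group | 0.302 | 0.166 / 0.166 | 5.2% |
| No filling | ANCOVA | 0.363 | 0.159 / 0.159 | 4.6% |

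In the ANCOVA, power is 0.62 without filling and 0.57 with overall-mean filling. The time × group mixed model on observed data only (250 runs, so a rough check) gave model SE 0.174 against empirical 0.175 with no effect, and type I error 3.6%.

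**With clustering.** Class-level t test, 10 classes of 30, ICC 0.05, 15% missing completely at random, 40,000 runs. The variance comes either from all five arms (5 df) or from the two compared arms only (2 df):

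| Filling | Type I error, 5 df | Type I error, 2 df |
|---|---|---|
| Arm mean | 8.2% | 6.6% |
| Class mean | about 5% | about 5% |
| Overall mean | about 5% | about 5% |

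Class-mean filling leaves each class mean unchanged, so a class-level test is unaffected. Overall-mean filling still reduces 0.36 to about 0.31 here.

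**Loss that depends on baseline and differs by arm (assumed).** In one arm, 30% of children below the baseline mean are lost and none above it; in the other, 15% are lost regardless of baseline. With no true effect:
- Arm-mean filling: spurious effect +0.08 SD; type I error 14.1% (ANCOVA), 11.1% (time × group).
- Overall-mean filling: about +0.07 SD; 7.6% and 7.3%.
- Observed-data ANCOVA with baseline: 0.00; 5.4%.

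**A child's adjacent visits.** If interpolation is meant literally, it cannot fill the last visit, or any visit of a child who has left for good. It is still a single value without uncertainty.

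**The case against.** The strongest reply is that the article does not say which mean, so no single harm can be asserted. That stands. Several stronger readings are tempting, and the article does not support them.

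- **That the rule both narrows intervals and biases effects.** When data are missing completely at random these belong to different means. Arm-mean filling inflates type I error but is unbiased; overall-mean filling attenuates the effect with type I error near nominal.
- **That every mean ignores baseline and class.** A class mean does not ignore class, and averaging a child's own visits does not ignore that child's level.
- **That the trial's false-positive rate will be 9.6%.** That figure describes an unclustered comparison of post values. Section 4.4 plans a clustered time-by-group model, and the results closer to it are 7.5% (unclustered) and 6.6% to 8.2% (class level).
- **That weaker children will drop out differentially.** Nothing in the article predicts this. Children may quit at any time (section 3.2.2), but section 3.3 plans steps to limit loss. The 0.07 to 0.08 SD is conditional on an assumed pattern.
- **That intention to treat is defeated.** Every enrolled child stays in the analysis; the fault lies in how missing values are represented.
- **That no imputation is needed at all.** This is true of missing outcomes in the mixed model. The adjusted models also need baseline values, and without a rule children who lack them would fall out.

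None of this rescues the rule. No reading carries imputation uncertainty, and leaving the mean open lets a later choice decide whether intervals narrow or effects shrink.

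**Conclusion.** The concern holds in a limited form. Section 3.2.2 prescribes single imputation by an unspecified mean, nothing elsewhere qualifies it, and the model already planned handles missing outcomes better.

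At 15% loss, missing completely at random, the consequence ranges from practically none (class mean, class-level test), through a type I error of about 6.6% to 8.2% in a class-level test or 7.5% in an unclustered time-by-group contrast (arm mean), to a 15% attenuation of the effect (overall mean). Bias beyond that requires loss that depends on baseline and differs by arm. The sizes rest on the assumed pre-post correlation of 0.6 in the pre/post simulations, on the plan's ICC of 0.05 and on classes as clusters in the class-level test. They illustrate the problem and do not predict this trial's error rate.

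**What to change.** In section 3.2.2, replace the mean-imputation rule for outcomes with a likelihood (REML) analysis of all observed assessments of all randomised children, using the mixed model and covariates already prespecified in section 4.4, and state the missing-at-random assumption. Do not simply delete the rule: name a method for missing baseline covariates, such as multiple imputation that respects the clustering. Add multilevel multiple imputation as a sensitivity analysis.

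No new data or children are needed. The cost is a little more analysis work and slightly wider intervals. Against arm-mean filling in the unclustered simulations, the reported SE rises by a factor of 0.174/0.166 = 1.05 (time × group) to 0.159/0.141 = 1.13 (ANCOVA), which is the uncertainty that filling had hidden.
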